#### Treatment models and primary treatment strategies

*Dialectical behavior therapy (DBT)* was developed by Marsha Linehan in the late 1980 from a CBT background and views emotional dysregulation as the core of BPD. Problematic behaviors, such as self-injury, suicide attempts, substance abuse, binge eating, dissociation, or impulsivity are dysfunctional ways of regulating emotions. Therefore, the primary focus of treatment is to teach patients functional skills to accept and regulate their emotions. The dialectical perspective underlying the therapeutic process simultaneously involves accepting current difficulties and changing the problem behavior through skills acquisition. DBT uses a broad range of cognitive and behavioral treatment techniques to foster skills acquisition.

In group sessions (‘skills training groups’), patients learn the four DBT modules (mindfulness, distress tolerance, emotion regulation, interpersonal effectiveness), which all seek to improve emotion regulation skills, and are encouraged to train these skills regularly.

The individual therapist supports the patient in implementing the skills that were learned in the group, assists with troubleshooting and removes obstacles to change. Problem behavior is worked through based on a target hierarchy that is organized according to the threat posed to the patient from the behavior and the general goals of DBT therapy. The highest priority is acute life-threatening behaviors and serious self-injuries. The second priority is for behaviors that impede the therapy, while the third priority area addresses behaviors that impair quality of life. Important change strategies include, for example, analyzing problem behavior using behavioral analysis, or teaching behavioral skills for emotion and stress regulation and interpersonal relationships. To improve self-regulation and awareness, patients maintain stress diaries, emotional logs and weekly diaries (“Diary Cards”). With contingency management, adaptive behaviors are reinforced while modifying problem behaviors.

DBT telephone coaching is provided in crisis situations. As such, the patient can call his individual therapist during a crisis and receive support in applying suitable skills. The therapists meet weekly to support each other in providing DBT in a DBT consultation team [22, 23, 55].

*Schema therapy (ST)*, developed by Jeffrey Young, like DBT has its roots in CBT, but also draws ideas and techniques of other theoretical orientations (e.g., attachment theory, psychodynamic and experiential therapies such as Gestalt therapy). ST assumes that aversive childhood experiences and the frustration of basic childhood needs (e.g., secure attachment, love, attention or autonomy) lead to the development of dysfunctional maladaptive schemas (basic mental representations of the self, relationships to others, and the world). To address the related emotional distress, early coping strategies (surrender, avoidance, overcompensation) are developed to block access to feelings and needs and hinder the development of healthy interpersonal skills and closeness. Subsequently, these needs cannot be met later in adult life.

BPD relies almost exclusively on the disorder-specific mode model [64]. A mode is a specific state that influences emotions, cognitions, bodily reactions and behaviors in a given situation. The following modes are characteristic of BPD: (A) *abandoned/abused child mode*, which is associated with strong emotions, such as sadness, loneliness and fears of abandonment; (B) the *angry, impulsive child mode* is reflected in angry outbursts, hostility or impulsive behaviors; (C) the *punitive parent mode* is characterized by self-hatred, shame, self-devaluation, and self-punishment; (D) the *detached protector mode*, in which BPD patients attempt to detach from emotional pain by maintaining distance from other people and avoiding or distracting from emotions with e.g., self-harm, dissociation, substance abuse, binge eating or social withdrawal; (E) the healthy modes (*healthy adult mode and happy child mode)*, which are often weak at the beginning of treatment. Additional maladaptive modes can be added to the participant’s mode case conceptualization as indicated (e.g., a patient with narcissistic traits might have an additional overcompensating coping mode in his/her case conceptualization), which will also be addressed in treatment.

The primary therapeutic goal of ST is to help patients to have their needs met in their current life and to change maladaptive schemas. To achieve this goal, specific tasks are pursued for every mode: care for, soothe and comfort the vulnerable child modes to meet frustrated needs; help the angry child modes deal with anger, combat the punitive parent and reassure the detached protector mode, so that the patients can reduce their avoidance strategies and learn healthier strategies for managing emotions and relationships. Ultimately, the most important goal is to strengthen the healthy modes during the entire treatment process.

To achieve these goals, there are cognitive, experiential, and behavior-oriented interventions, and the working alliance is specifically designed as ‘limited reparenting.’ This suggests that the therapist –within the boundaries of a professional therapeutic relationship- behaves as a ‘good parent’ towards the patient to create an antidote for aversive interpersonal childhood experiences. Similarly, the ST group is designed as a ‘group family’ with the patients as the ‘siblings’ and the two therapists as the ‘parents’ [24, 25, 55].

#### Similarities and differences between DBT and ST

Both treatments share a cognitive-behavioral background, however; the approach is very different in practice. The primary differences are: In DBT, skills for stress and emotion regulation, mindfulness and interpersonal skills are taught using cognitive and behavior-oriented therapeutic techniques and the primary treatment focus is on the present. Patients are encouraged to practice the new strategies on a regular basis. In contrast, ST has a strong emphasis on early development and experiential techniques, such as imagery rescripting and chair dialogues, which are extensively used to change the patient’s emotional experiences. The DBT therapist acts as a ‘coach’ for the patient, while the ST therapist acts, to a limited extent, as a ‘good parent’ and uses interpersonal problem patterns that arise within the therapeutic relationship to change modes. For a detailed description of the similarities and differences between DBT and ST see [55]. Table 1 summarizes the main differences between the two methods.

**Table 1 Tab1:** Main differences between Dialectical Behavior Therapy (DBT) and Schema therapy (ST)

	DBT	ST
Case conceptualization	Focus on connection between emotion regulation skills deficit and dysfunctional behavior; emotion dysregulation is the central problem	Case conceptualization uses the mode concept; the frustration of basic needs and trauma in childhood leads to the development of maladaptive schemas and modes. For each individual, there is a case conceptualization in schema mode terms that fits the patient’s profile.
Focus on childhood experiences	Primary focus on the present, focus on childhood experiences mainly in the context of validating emotional difficulties (level 4 validation)	Full integration: Current problems are associated with childhood experiences; psychoeducation for basic needs, the development of schemas and modes, emotionally processing aversive childhood memories to change the meaning of early experiences that underlie the schemas
Trained skills	Emotion regulation, stress tolerance, mindfulness, interpersonal skills	Awareness of one’s own needs, schemas and modes. Although the functional expression of emotions, needs and assertiveness is encouraged, there is no explicit skill training in these areas.
General therapeutic strategies	Validation strategies Commitment strategies Dialectical strategies (balance between acceptance and change, pro-contra lists) Major use of cognitive and behavioral techniques	Special focus on experiential (esp. imagery rescripting and chair-dialogues) and relational techniques (limited reparenting, empathetic confrontation) Mode-specific use of cognitive and behavioral techniques
Analysis of problem behaviors	Chain analysis based on the DBT model for each type of problem behavior; hierarchy of problem behaviors; focus on obvious and threatening problem behaviors, such as suicide attempts, self-harm and impulsive behavior	Mode analysis/chair dialogues or imagery work to understand problematic situations from the perspective of the mode model, focus on obvious problem behavior, as well as “hidden” problem behaviors, such as avoidance or surrender
Structure of the individual therapy session	Fixed structure with a “crisp beginning” that includes a diary card, processing topics according to the DBT goal hierarchy, and focusing on emotions	No fixed structure specification, flexible hierarchy depending on the dominating mode and the frustrated needs
Structure of the group session	Homework and goal-related opening and closing rounds, teaching skills from the DBT modules with a fixed manual; focus on cognitive and behavioral therapeutic techniques	Begins with safety imagery, topics depend on the dominating mode; designed as a “group family” to create corrective experiences; a primary focus on experiential and relational techniques
Addressing self-injury	Fixed procedures according to protocol based strategies, top priority in goal hierarchy; self-injuries are usually discussed with behavioral analysis before addressing other issues	No fixed structure specification, and does not need to be treated as a first priority (only if highly threatening); therapeutic intervention is directed at the mode that underlies the self-injury
Addressing interpersonal problems of the patient	Psychoeducation for interpersonal skills; behavioral training with standard and individual role-play exercises	Understanding interpersonal problems by using the mode model; interpersonal problem patterns normally also arise in the therapeutic relationship and are directly addressed, focus on expressing ones’ own needs and emotions; role-plays as needed but often in a later stage of therapy
Addressing emotional problems	Comprehensive psychoeducation in the modules for emotional management; mindfulness and acceptance of emotions; decisions about whether one should act according to or opposite from the emotion; emotion processing with the help of emotion protocols (cognitive approach)	Promotes experiencing emotions in a safe way; focus on needs (e.g., “What do I need when I’m sad?”); validating emotions and needs, when possible, fulfilling the need through limited reparenting, the empathetic confrontation of experiential avoidance that is displayed in the coping modes, experiential interventions, primarily imagery rescripting and chair dialogues, aim to develop corrective experiences
Developing the working alliance	Therapist acts as a ‘coach’ for the patient; the therapeutic team is at eye level with patient	Therapist acts, to a limited extent, as a ‘good parent’ with ‘limited reparenting’; uses the working alliance to change modes
Mindfulness training	Central role; non-judgmental attitude is promoted	Not included in ST
Skills training in distress tolerance	High priority; psychoeducation, developing a skills chain for stress regulation	Limited use, primarily for emergency situations at the beginning of therapy

### Clinical effectiveness study

#### Assessment and outcome measures

Before randomization, the patients are assessed at baseline. Baseline assessments are conducted at four assessment points over a period of approximately three months with one assessment point (assessing BPD severity and costs) directly before randomization. However, the timing of the baseline assessments will be adjusted based on the availability of treatment vacancies, e.g., if a treatment slot is available, the baseline assessment can be moved to a minimum time of one month to include the patient. On the other side, there can be a waitlist for inclusion and the baseline assessments will be performed over a longer time, with a maximum of a one year wait for treatment initiation. In this case, at the start of the waiting period, a check of in- and exclusion criteria is done, baseline assessments are performed not longer than six months ahead of treatment start. A re-assessment of the primary outcome, the interview for BPD severity, is performed, if the first baseline assessment of these measures is longer than three months ahead of treatment start. Assessments include PC-based questionnaires and semi-structured interviews. At baseline, in addition to the measures that are described below, there is a demographic questionnaire and the Childhood Trauma Questionnaire (CTQ). The CTQ assesses self-report childhood maltreatment experiences across five dimensions: emotional, physical, and sexual abuse as well as emotional and physical neglect. The original version and the German translation have good psychometric properties [65, 66].

Data are assessed at baseline and 6 (M1), 12 (M2) and 18 months (M3) after treatment initiation and 6 (M4), 12 (M5) and 24 months (M6) after the end of therapy for a naturalistic follow-up. An overview of the instruments at each assessment point is provided in Table 2.

**Table 2 Tab2:** Instruments at each assessment

	Baseline^b^	Assessment points during the treatment program			Assessment points during Follow-up		
		6 months	12 months	18 months	6 months	12 months	24 months
BPDSI-IV	**••**	**•**	**•**	**•**	**•**	**•**	**•**
SCID I	**•**			**•**		**•**	**•**
SCID II	**•**			**•**		**•**	**•**
CTQ	**•**						
Demographics	**•**			**•**		**•**	**•**
WHODAS 2.0	**••**	**•**	**•**	**•**	**•**	**•**	**•**
WSAS	**•**	**•**	**•**	**•**	**•**	**•**	**•**
EuroQol-5D	**•**	**•**	**•**	**•**	**•**	**•**	**•**
WHOQOL-	**•**	**•**	**•**	**•**	**•**	**•**	**•**
BPD	**•**	**•**	**•**	**•**	**•**	**•**	**•**
QTF	**•**	**•**	**•**	**•**	**•**	**•**	**•**
DSS	**•**	**•**	**•**	**•**	**•**	**•**	**•**
BSI	**•**	**•**	**•**	**•**	**•**	**•**	**•**
QIDS	**•**	**•**	**•**	**•**	**•**	**•**	**•**
DERS	**•**	**•**	**•**	**•**	**•**	**•**	**•**
RSQ	**•**	**•**	**•**	**•**	**•**	**•**	**•**
WAI	**•** ^a^	**•**	**•**	**•**	**•**	**•**	**•**
DBT-WCCL	**•**	**•**	**•**	**•**	**•**	**•**	**•**
YSQ	**•**	**•**	**•**	**•**	**•**	**•**	**•**
SMI	**•**	**•**	**•**	**•**	**•**	**•**	**•**
Cost interview	**•**	**•**	**•**	**•**	**•**	**•**	**•**

*Abbreviations*: *BPDSI-IV*=Borderline Personality Disorder Severity Index version IV, SCID I=Structured Clinical Interview for DSM-IV Axis-I Disorders, SCID-II=Structured Clinical Interview for DSM-IV Axis-II Disorders, *CTQ* = Childhood Trauma Questionnaire, *WHODAS 2.0* = World Health Organization Disability Assessment Schedule 2.0, *WSAS* = Work and Social Adjustment Scale, EuroQol-5D = European Quality of Life questionnaire-5 dimensions, *WHOQOL* = World Health Organization Quality of Life questionnaire, *BPD* = Borderline Personality Disorder checklist, *QTF* = Questionnaire of thoughts and feelings, *BSI*=Brief Symptom Inventory, *QIDS* = Quick Inventory of Depressive Symptomatology, *DERS* = Difficulties in Emotion Regulation Scale, *RSQ* = Rejection Sensitivity Questionnaire, *WAI* = Working Alliance Inventory, applied in an individual and a group version

^a^assessed after third session, *DBT-WCCL* = Dialectical Behavior Therapy Ways of Coping Checklist, *YSQ* = Young Schema Questionnaire, *SMI*=Schema Mode Inventory

^b^Baseline consists of five assessments

•Instrument is assessed at the respective assessment point, ••BPDSI, WHODAS 2.0 are assessed twice at baseline

Due to the long duration of the study a team of blind raters will be needed to cover all assessments. The rater team consists of clinical psychologists with a completed further education in psychotherapy or an advanced state of this education as well as master students of clinical psychology who receive standardized training for the primary outcome interview and the WHO global functioning interview (WHODAS). The training for students and new clinical psychologists includes 2 to 3 interview sessions as an observer and a minimum of 2 interview sessions under life-supervision. Raters are only allowed to start with self-dependent interviews if the differences in ratings are reduced to a maximum of a one point difference not exceeding three items, and the performance of the interview is correct. Regular supervision will be offered for the raters as well as re-analyses of audio recordings to keep up the inter-rater reliability. The comorbid diagnosis will be assessed with the SCID I and II by clinical psychologists with a completed further education in psychotherapy or are in an advanced state of this education. These raters are well experienced in the use of the SCID due to specific SCID training and to their clinical practice. Participants and their therapists are informed of the participants’ scores on all instruments except for the cost assessment and the working alliance inventory (so that patients also report negative feelings towards their therapists). This is standing practice (regularly assessing progress or lack of progress) and is used as feedback to help to improve treatment.

##### Primary outcome measure

The primary outcome is BPD severity, which is assessed with the total score of the *Borderline Personality Disorder Severity Index version IV (BPDSI-IV)*, a semi-structured interview that rates all facets of BPD pathology. It assesses frequency and severity for the 9 DSM-IV BPD symptoms over the prior three months. The total score ranges from 0 to 90. The scores on the BPDSI-IV subscales provide information on the severity of each of the nine dimensions of BPD. The BPDSI-IV has excellent psychometric features (Cronbach’s alpha = .85; interrater reliability .99, high validity and sensitivity to change) [67, 68]. A cutoff of 15 points has been empirically shown to differentiate people who have BPD from people who do not have BPD; our inclusion criterion of > 20 has been used in several studies [45, 47, 50], as it reliably distinguished BPD from non-BPD PDs, and indicates severe BPD that is in need of treatment.

##### Secondary outcome measure

Secondary outcomes are assessed through interviews and self-report:

Psychosocial Functioning and Participation is administered as an interview and is assessed with the *World Health Organization Disability Assessment Schedule 2.0 (WHODAS 2.0)* [69], a general measure of functioning and disability in major life domains, including understanding and communication, getting around, self-care, getting along with others, life activities and participation in society. In addition, the *Work and Social Adjustment Scale (WSAS)* [70] a self-report instrument that assesses functional impairment in the domains of work, household, social leisure, private leisure, family, and relationships is used. The WSAS is reliable, valid and change-sensitive with different patient samples [71, 72].

Quality of life is assessed with two, well-established self-report questionnaires: the World Health Organization Quality of Life Questionnaire (WHOQol) [73] and the EuroQol-5D (EQ-5D) [74]. The WHOQol is a valid and reliable measure that assesses the quality of life in the two weeks prior the assessment for several domains (physical health, psychological health, social relationships, environment, positive feelings, negative feelings, and self-esteem). The EQ-5D measures health-related quality of life on five dimensions (mobility, self-care, activity, pain/discomfort and anxiety/depression). For the cost-utility analysis (see below), the profiles from these five health-related dimensions are assigned a value based on the social tariffs of the EQ-5D, the EQ-5D UK value set [75], to generate utilities. A German value set will be used if it becomes available. Utilities reflect a population’s preference for a specific set of health outcomes. The utilities from different time points are used to compute quality-adjusted live years (QALY) by multiplying the change in utility between the assessments by the duration of the period between the assessments. In addition, the EuroQol thermometer assigns a score that is between 0 and 100 for participant’s current subjective health status.

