#### Sample size

The primary variable for calculating the sample size is the BPDSI total score. The sample size calculation is based on the number of participants that are needed to detect a clinically significant difference between the two conditions. Although the meta-analyses on DBT demonstrated global changes in effect sizes (ES) of d = 0.5 [27] and ST had a higher change in ES for borderline-specific symptoms (d = 2,96 [45] and d = 2.81 [44]), these cannot reliably be compared because they reflect different samples and outcome instruments, and there has been no direct comparison between the two methods. Therefore, we chose a medium ES of d = 0.5 for detecting group differences for the sample size calculation. Detecting a difference with this ES could strongly influence clinical decision making. As such, *n* = 64 patients per condition are required to detect group differences with a Type I error of 5% and a power of 80% (Type II error = 20%). Assuming an attrition rate of 20%, we will recruit *n* = 160 patients.

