#### Cost calculation and efficiency analysis

Costs are expressed in Euros using the 2015 price level. To calculate direct costs, we multiply resources by their corresponding unit cost (i.e., the cost of a particular medical or non-medical treatment). In contrast to other countries, such as Great Britain, there is no obligatory unit cost list in Germany. In the current study, unit costs are calculated based on Bock et al.’s [96] recent proposals. Bock et al. provided unit costs from a societal perspective for resources, including inpatient and outpatient medical care. Additionally, the authors showed how to update those unit costs on a yearly basis using regularly published sources. Indirect Costs are calculated according to the Human Capital Approach. Compared to the Friction Cost method, the Human Capital Approach is more applicable to BPD patients [97] because a sizable proportion of BPD patients are work disabled and work disability is not counted in the Friction Cost Method. We count productivity loss due to absences from paid work and productivity losses due to work disability. For patients with a paid job, we multiply the days absent from work by individual labor costs. Work disability-related costs are calculated based on the assumption that patients without BPD would pursue a paid job. Therefore, we multiply the national average monthly labor costs by the number of months that the patients were work-disabled.

The economic analysis is also based on the intention-to-treat principle. To determine the efficiency of DBT and ST, we will perform cost-effectiveness and cost-utility analyses. We will calculate two incremental cost-effectiveness ratios (ICER; the difference in costs between the two interventions divided by their difference in effectiveness). In the context of the cost-effectiveness analysis, we will calculate the costs per 10 BPDSI improvement points. For the cost-utility analysis, the costs per quality adjusted live years (QALY) will be calculated based on the EQ-5D questionnaire.

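### The stated QALY rule (change in utility times interval length) does not give QALYs and can reverse which arm appears to gain more

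*Protocol article*

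**What the plan says.** The quality-of-life paragraph under Secondary outcome measure in the protocol article says: "The utilities from different time points are used to compute quality-adjusted live years (QALY"), and gives the calculation: "by multiplying the change in utility between the assessments by the duration of the period between the assessments".

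Cost calculation and efficiency analysis then uses the result: "For the cost-utility analysis, the costs per quality adjusted live years (QALY) will be calculated based on the EQ-5D questionnaire". It defines the incremental ratio as "the difference in costs between the two interventions divided by their difference in effectiveness". Two such ratios are planned, one per 10 BPDSI points and one per QALY.

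The visit times are in Assessment and outcome measures: "Data are assessed at baseline and 6 (M1), 12 (M2) and 18 months (M3) after treatment initiation", then "6 (M4), 12 (M5) and 24 months (M6) after the end of therapy for a naturalistic follow-up". Table 2 lists the EQ-5D at every one of these visits. Nowhere does the article mention area under the curve, mean utility over an interval, or change from baseline, so nothing corrects the sentence.

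**The concern.** The sentence fixes a formula, and the formula leaves out the level of utility. Three things follow if it is applied as written:

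- A patient whose utility never changes accrues zero QALYs, whether that utility is 0.5 or 0.9.
- An improvement is credited only in the interval in which it appears. Holding it for years adds nothing.
- The credit depends on the length of that interval. The last interval is 12 months and the others are 6, so the same improvement counts double if it first shows at the final visit.

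The cost-utility ratio divides by the difference between arms in this quantity. A denominator of the wrong size misstates the cost per QALY. A denominator of the wrong sign makes the better arm look worse. The trial follows patients for two years after therapy to examine lasting effects, and a measure that gives no credit for lasting benefit works against that purpose.

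**Working it through.** The article gives no QALY figure to reproduce, so the check applies the written rule and the area under the curve to the same utility paths.

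**Inputs from the article.** With therapy ending at 18 months, the visits fall at 0, 6, 12, 18, 24, 30 and 42 months. The interval lengths are 0.5, 0.5, 0.5, 0.5, 0.5 and 1.0 years, 3.5 years in all.

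**Assumptions.** The utilities are illustrative, since the article reports none. Baseline is placed at month 0. The main example uses the full 42 months; an 18-month version follows.

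**Formulas**, with `u` the utility and `t` the time in years:

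- As written: sum over intervals of `(u_end − u_start) × (t_end − t_start)`
- Area under the curve: sum over intervals of `(u_start + u_end)/2 × (t_end − t_start)`
- True gain: the area minus the area for staying at the baseline utility. At 0.5 throughout, that is 0.5 × 3.5 = 1.75.

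**Early, sustained gain** (0.5 at baseline, 0.7 from month 6 on)

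- As written: 0.2 × 0.5 = 0.10; every later interval contributes 0.
- Area: 0.6 × 0.5 + 0.7 × 3.0 = 0.30 + 2.10 = 2.40. Gain 2.40 − 1.75 = 0.65.

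**Late gain** (0.5 to month 30, 0.7 at month 42)

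- As written: 0.2 × 1.0 = 0.20.
- Area: 0.5 × 2.5 + 0.6 × 1.0 = 1.25 + 0.60 = 1.85. Gain 1.85 − 1.75 = 0.10.

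**Gain held, then lost** (0.7 from month 6 to month 30, back to 0.5 at month 42)

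- As written: 0.2 × 0.5 − 0.2 × 1.0 = −0.10.
- Area: 0.30 + 0.7 × 2.0 + 0.6 × 1.0 = 2.30. Gain 2.30 − 1.75 = 0.55.

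| Path over 42 months | As written | True gain |
|---|---|---|
| Early, sustained | 0.10 | 0.65 |
| Late only | 0.20 | 0.10 |
| Held, then lost | −0.10 | 0.55 |

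If one arm followed the early path and the other the late path, the true denominator is 0.65 − 0.10 = 0.55 in favour of the early arm. The written rule gives 0.10 − 0.20 = −0.10. The sign is reversed.

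If the comparison arm stayed at 0.5, the sign is right but the size is not. The rule gives 0.10 at every horizon, while the true gain is 0.25 at 18 months, 0.45 at 30 and 0.65 at 42. The cost per QALY would be overstated 2.5-, 4.5- and 6.5-fold.

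**Eighteen months only.** All intervals are 0.5 years, so the rule collapses to 0.5 × (utility at month 18 − utility at baseline) and the visits in between drop out.

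- Path 0.50, 0.70, 0.70, 0.65: rule 0.5 × 0.15 = 0.075. Area 0.30 + 0.35 + 0.3375 = 0.9875, less 0.75 for staying at 0.50, gives a gain of 0.2375.
- Path 0.50, 0.50, 0.50, 0.70: rule 0.5 × 0.20 = 0.10. Area 0.25 + 0.25 + 0.30 = 0.80, less 0.75, gives a gain of 0.05.

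The ranking reverses here too, without the 12-month interval.

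**The case against.** The strongest defence is loose wording. The clause sits in an instrument description, and the authors may have meant change from baseline. Change from baseline at each visit times the preceding interval gives 0.2 × 3.5 = 0.70 for the early path and 0.2 × 1.0 = 0.20 for the late path. That is the right order and near the true 0.65 and 0.10. However, the sentence says the change is between assessments, and no other passage points to baseline. A third reading, first-to-last change times total duration, gives 0.2 × 3.5 = 0.70 for both paths and hides the difference of 0.55. What stands is that the error is certain only if the sentence is applied as written.

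Four narrower points also have weight:

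- The preference for late change comes only from the final 12-month interval. Up to month 30 the intervals are equal and the rule is indifferent to timing. The 18-month example shows that reversal does not need the long interval.
- The 42-month contrast is extreme for two active treatments. The 18-month paths are milder and still reverse.
- The zero score for a stable patient (at 0.8, for instance, the true total is 0.8 × 3.5 = 2.80) shows that the quantity is not a QALY. It is not by itself an error in the ratio, because equal constant levels cancel between arms.
- Only a secondary economic result is touched. The BPDSI analysis, the sample size, the cost data and the cost per 10 BPDSI points do not depend on it, and the correction can still be made at analysis.

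**Conclusion.** The concern holds. The QALY rule is wrong as written. This is a stated formula, not detail left to a fuller document, and nothing else in the article overrides it. On the trial's schedule it credits an early, sustained gain of 0.20 in utility with 0.10 instead of 0.65 QALY over 42 months, and it can reverse the order of the arms over either 42 or 18 months. These sizes rest on assumed utilities, baseline at month 0 and therapy ending at 18 months. That the formula omits the level of utility does not depend on those assumptions. The consequence is confined to the cost-utility analysis, but there it can change the conclusion, so the sentence must be corrected before that analysis is run.

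**What to change.** Replace the sentence with: QALYs are the area under the EQ-5D utility curve, calculated as the sum over intervals of (u1 + u2)/2 times the interval length in years. State the period over which they are accumulated.

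Estimate the difference between arms by regression with baseline utility as a covariate. Once levels enter the calculation, a chance difference at baseline carries through every interval. An assumed difference of 0.05, for example, would amount to 0.05 × 3.5 = 0.175 QALY over 42 months. If an analysis plan already specifies the area under the curve and this adjustment, the article's sentence only needs to be brought into line with it.

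The cost is one sentence and one line of code. The EQ-5D is already collected at baseline and at every later visit, so no new data are needed.
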